### Selection Criteria for Quantitative Data

#### Inclusion Criteria

i. CLHIV and CHEU aged 1 month to 5 years admitted at Mwanamugimu Nutrition Unit with severe acute malnutrition.ii. For prevalence of HIV-infection sub-study, children presenting with severe acute malnutrition on admission at Mwanamugimu Nutrition Unit.iii. For PK sub-study, the child should have been on lopinavir containing antiretroviral therapy for at least 2 weeks and should have been in hospital for at least 1 week; and on ready to use therapeutic feeds (RUTF).iv. Parent or guardian provides informed consent, including consent for HIV testing.

#### Exclusion Criteria

a. Readmission for management of severe acute malnutrition.

For PK sub-study;

b. A child with documented poor adherence to antiretroviral therapy.c. A child on anti – TB medication.d. A child known to have vomited the drug on the sampling day.

### Selection Criteria for Qualitative Data

#### Inclusion Criteria

i. Mothers of CLHIV with severe acute malnutrition.ii. Provision of informed consent.

#### Exclusion Criteria

a. Inability to undergo in-depth interviews, for such reasons as illness and unavailability.

### Study Procedures

All severely malnourished children and their mothers will have rapid HIV antibody tests on admission as per routine practice; at least 280 children will participate in the cross-sectional study. Children under 18 months of age with positive HIV results will have blood taken for DNA PCR. The children who test positive or whose mother's test positive (i.e., are CHEU) will be eligible for enrolment into the trial. Participant enrolment will be done between 9.00 am and 4.00 pm from Monday to Friday to allow for blood samples to be taken to the laboratories on the day of enrolment. HIV rapid testing will be done at the unit (Mwanamugimu); HIV DNA PCR at the Baylor Uganda center of excellence (COE) laboratory at the Mulago Hospital Complex. At enrolment, anthropometry and a physical examination will be done; resuscitation will be provided as needed and a blood sample will be taken off for blood culture. The blood culture and sensitivity will be done in the Microbiology laboratory at the Makerere University College of health Sciences (MakCHS). After all enrolment procedures have been done, children will be randomized to ceftriaxone vs. ampicillin/gentamicin. The children will then receive antibiotics as randomized for 1 week together with other routine care. At day 8 (on completion of study medication), the children will be evaluated to ascertain any events that may have occurred and document administration of the study medication. They will then be followed up until discharge/death whichever occurs first. ART naïve CLHIV will initiate ART during admission while ART-experienced children will continue their regimens; both groups will receive daily cotrimoxazole throughout follow-up. The eligible CLHIV on LPV/r (target number – 76) will have 3 sparse PK samples taken at least 2 weeks after ART initiation and at least 1 week after admission to hospital (after they have completed the stabilization phase of treatment); the samples will be taken over 2–3 days depending on what is physiologically possible for the children. The samples will be collected from the study population to cover three time points. The child will take an observed morning dose and then sampling will be done at 3 h, at 6 h and at 12 h (just before the evening dose). LPV concentrations in the plasma samples will be determined using ultra performance liquid chromatography with ultraviolet detection in the Department of Pharmacology and Therapeutics, MakCHS. All laboratories are on the same location on Mulago hill, within a 1 km radius. During admission, the mothers will be interviewed to ascertain sociocultural/ system factors related to antenatal care attendance, prior HIV testing, knowledge and access to PMTCT services, infant feeding practice and ART adherence (theirs and the children's as applicable). Some of the mothers (~20) will be asked to participate in in-depth interviews. These will be consecutively enrolled until data saturation. These interviews will be tape recorded, transcribed verbatim and then translated into English where applicable. Any adverse events that develop will be managed according to the treatment protocols of Mwanamugimu Nutrition Unit/ Mulago Hospital. The principal investigator will be notified of these events within 24 h, who will in turn inform the trial sponsor within 24 h; and the Research Ethical Committee (School of Medicine Research Ethical Committee at Makerere University) within 7 days; and Uganda National Drug Authority within 7 days, as per the local research guidelines.

The procedures, which will be performed by a study doctor, a study nurse and a study counselor trained on the study protocol, are summarized in the trial schema (Table 1).

**Table 1 T1:** Redmothiv trial schema.

**Assessments/ procedures**	**Days in trial**									
	**Screening**	**Randomization (day1)**	**Daily until day 7**	**Day 8**	**At discharge or death**	**PK day 1**	**PK day 2**	**PK day 3**	**Qualitative study day**	**Acute event**

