**Methods:**

This is an open label randomized controlled trial involving 300 children; 76 CLHIV and 224 CHEU. The participants are being randomized to receive 1 week of ceftriaxone (*n* = 150) or standard-of-care (ampicillin/gentamicin) (*n* = 150), in addition to other routine care. The trial's primary outcome is in-hospital mortality. Secondary outcomes are: length of hospitalization; weight-for-height, weight-for-age and height-for-age z-scores; and pattern/antimicrobial sensitivity of pathogens. In addition, 280 severely malnourished children of unknown serostatus will be tested for HIV at admission to determine the prevalence and factors associated with HIV-infection. Furthermore, all the CLHIV on LPV/r will each provide sparse pharmacokinetic (PK) samples to evaluate the PK of LPV/r among malnourished children. In this PK sub-study, geometric means of steady-state LPV PK parameters [Area Under the Curve (AUC) _0−12*h*_, maximum concentration (C_max_) and concentration at 12 h after dose (C_12h_)] will be determined. They will then be put in pharmacokinetic-pharmacodynamic (PK-PD) models to determine optimal doses for the study population.

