### Study Population

Three hundred children aged 1 month to 5 years (76 CLHIV and 224 CHEU) whose caretakers provide informed consent will be randomized to receive ceftriaxone (*n* = 150) or ampicillin plus gentamicin (*n* = 150). The 1 month to 5-year age group has been selected because it is the most affected by severe acute malnutrition and constitutes over 95% of admissions at Mwanamugimu Nutrition Unit. Also, the 1:3 ratio of CLHIV to CHEU in this sample is reflective of the current proportions of CLHIV and CHEU admitted at Mwanamugimu Nutrition Unit.

Three hundred randomized children provide >80% power to detect reductions in mortality from 28% (average across CLHIV and CHEU in preliminary audits at the unit) to 14% (50% relative reduction; absolute 14% improvement), allowing for 10% non-compliance/loss-to-follow-up (leaving hospital without official discharge) in each group. When half the participants have been enrolled (*n* = 150), the data safety monitoring board (DSMB) will review the preliminary data to determine if these estimates are appropriate. In addition, at least 280 severely malnourished children and their mothers will be tested for HIV at admission; any positive children will also be eligible to participate in the clinical trial. Two hundred eighty children provide 80% power to determine the prevalence of HIV-infection, using the prevalence of HIV-infection of 24% obtained in the probisam study in Mwanamugimu in 2013 (10), as a reference. The CLHIV in the clinical trial on LPV/r will take part in the pharmacokinetic sub-study providing 3 sparse PK samples each.

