### Data Management and Statistical Analysis

A database will be designed to capture the patient data from the study tools. Data will be checked for completeness before entry into the database. The database will be backed up on a daily basis. The study tools for each patient will be put in separate folders and kept in lockable cabinets. The primary outcome will be in hospital mortality. Secondary outcomes will be: length of hospitalization (for those that are followed up till discharge); as well as weight-for-height, weight-for-age and height-for-age z-scores during follow up. The change in these anthropometric indices (z-scores) from admission to discharge will be determined, while controlling for the number of days of hospitalization. Another secondary outcome will be the distribution/antimicrobial sensitivity of pathogens.

Mortality (and other time-to-event data) will be compared between randomized groups using Kaplan Meier curves and Cox proportional hazards regression. WHO reference ranges will be employed to determine the anthropometric z-scores which will be analyzed using linear regression. Other categorical factors will be compared between randomized groups using chi-squared and exact tests, and continuous data using rank-sum tests. The statistical analyses will be performed in STATA version 15 (Stata Corporation, Houston, Texas).

Qualitative data from the in-depth interviews of the mothers will be analyzed using a content thematic approach, using *NVivo software*. We will enroll mothers and perform ongoing analysis until there is saturation of data.

For primary analysis in the PK sub study, sparse PK samples will be obtained from approximately 76 CLHIV. Using NONMEM version 7.3, PK-PD modeling and simulations will be performed to determine primary PK parameters, measures of plasma drug exposure and the dosing requirements.

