Malnourished CLHIV have been reported to have poor outcomes on ART (11, 12); part of the explanation could be that the doses of antiretroviral drugs determined with well-nourished children may not be appropriate for the severely malnourished children who are known to have an altered physiology. For example, the drug levels in individuals are affected by the protein binding capacity of the drugs and it is known that malnourished children have low levels of protein (albumin) (25), implying that for the drugs that are highly bound to protein there would be a lot of free drug in malnourished children with a potential to cause an excess of adverse events. Examples of such drugs are lopinavir and ritonavir which are 98–99% bound to the blood plasma proteins albumin and alpha-1-acid glycoprotein (26). The Ugandan recommended alternative first line ART regimen for HIV infected children, is abacavir+lamivudine+lopinavir/ritonavir. Lopinavir/ritonavir (LPV/r) is also a key alternative drug in second-line regimens (18). In this project, we will investigate the pharmacokinetics of LPV/r among the severely malnourished children on ART, thereby providing an opportunity to test the hypothesis that severely malnourished children are ineffectively dosed according to the Ugandan guidelines, which does not differentiate well-nourished from malnourished children. It is possible that the severely malnourished children are exposed to toxic levels of free drug given the low level of albumin and drugs with high protein binding capacity. We will obtain sparse PK samples from the children while stable, likely in the second week of hospitalization, with the volumes of blood collected being those that are physiologically safe, such as those provided in a review of safe limits to volume by Howie SR (21). The study will also build on the work on PK and acceptability of LPV/r pellets in the CHAPAS 2 trial where bioequivalence between the pellets and syrup was demonstrated and the pellets were highly acceptable (27) and the follow on and ongoing implementation study of the LPV/r pellets (LIVING study) (28); as well as the LOLIPOP study evaluating the PK and acceptability of the 4 in 1 (abacavir+lamivudine+lopinavir/ritonavir) sprinkle formulation (29). Dolutegravir based regimens are becoming increasingly available and it is possible during the study period there are children that will be on dolutegravir. Dolutegravir PK will be considered among these children.

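### The pharmacokinetic target of 76 children equals the trial's whole planned enrolment of children living with HIV, with no allowance for deaths, exits, regimen or eligibility

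*Protocol article*

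**What the plan says.** The Abstract gives the composition of the trial: "This is an open label randomized controlled trial involving 300 children; 76 CLHIV and 224 CHEU". Study Population repeats it ("Three hundred children aged 1 month to 5 years (76 CLHIV and 224 CHEU") and explains the split: "the 1:3 ratio of CLHIV to CHEU in this sample is reflective of the current proportions". Study Design places the PK sub-study inside the trial, so it has no other source of children.

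Study Procedures then give the sub-study's target: "The eligible CLHIV on LPV/r (target number – 76". Data Management and Statistical Analysis plans on the same number: "sparse PK samples will be obtained from approximately 76 CLHIV".

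The same article describes several ways in which a randomized child can fail to reach PK sampling:

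- **Death.** Study Population plans on in-hospital mortality of 28% against 14%. The Introduction cites 33% and 47% among CLHIV at this unit in two earlier studies.
- **Exit.** Study Population allows 10% per group for non-compliance or leaving without discharge.
- **Regimen.** The Introduction and Discussion call LPV/r an alternative drug. The Discussion adds: "Dolutegravir based regimens are becoming increasingly available".
- **Criteria.** Under Inclusion Criteria, "the child should have been on lopinavir containing antiretroviral therapy for at least 2 weeks"; the child must also have spent a week in hospital and be on therapeutic feeds. Exclusion Criteria remove children with documented poor adherence, on TB treatment, or known to have vomited the drug on the sampling day.

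On timing, the Discussion says: "We will obtain sparse PK samples from the children while stable, likely in the second week of hospitalization". Study Procedures say that ART-naive children start ART during admission, and that follow-up ends at discharge or death.

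**The concern.** One number serves as both the count at randomization and the count at PK sampling. The two can be equal only if nobody is lost in between. Yet death in hospital is the trial's primary outcome, and the main sample size already allows for exits.

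At stake is how firmly the PK results can be stated. The Abstract promises geometric means of exposure parameters and then models to find optimal doses for the study population. If fewer children contribute, those estimates will be less precise than a reader who takes 76 at face value would expect. The contributors will also be a selected group: children past stabilization, on LPV/r and without documented poor adherence. The primary mortality comparison is not affected.

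**Working it through.** **Where 76 comes from.** The article shows no PK sample-size calculation. The number matches the trial's CLHIV total: at a 1:3 ratio, 300 / 4 = 75, against 76 stated. The implied carry-through from randomization to PK sampling is 76 / 76 = 100%.

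**Inputs, all from the article.** CLHIV randomized: 76. Planned mortality: 28% and 14%, which with equal arms averages (28 + 14) / 2 = 21%. Earlier CLHIV mortality: 33% and 47%. Non-compliance or loss: 10%.

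**Children left after deaths and loss**, before any regimen or eligibility loss: n = 76 × (1 − mortality) × 0.90. The last column is the ratio of log-scale confidence-interval widths, √(76 / n). It assumes the same between-child spread and ignores the small change in the t quantile.

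| Mortality | Calculation | n | Width relative to 76 |
|---|---|---|---|
| 14% | 76 × 0.86 × 0.90 | 58.8 | 1.14 |
| 21% | 76 × 0.79 × 0.90 | 54.0 | 1.19 |
| 28% | 76 × 0.72 × 0.90 | 49.2 | 1.24 |
| 33% | 76 × 0.67 × 0.90 | 45.8 | 1.29 |
| 47% | 76 × 0.53 × 0.90 | 36.3 | 1.45 |

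**Sensitivity to the approximations.**

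- If the 10% is ignored altogether, because part of it is non-compliance rather than exit: 76 × 0.86 = 65.4, 76 × 0.79 = 60.0 and 76 × 0.72 = 54.7.
- If, as an assumption, only half of the deaths and half of the losses at 21% mortality come before sampling: 76 × (1 − 0.105) × (1 − 0.05) = 64.6.

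Even these lenient versions fall more than 10 short of 76.

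**Regimen and eligibility.** The article gives no share of CLHIV on LPV/r, ART-naive, on TB treatment or poorly adherent, so I put no number on this step. It can only reduce the counts.

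**Enrolment needed to sample 76**, if every remaining child were on LPV/r and eligible: 76 / (0.79 × 0.90) = 106.9, so 107 CLHIV at 21% mortality; 76 / (0.72 × 0.90) = 117.3, so 118 at 28%.

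**Timing for ART-naive children.** ART started on day 1 at the earliest reaches two full weeks at about day 15. The second week of hospitalization is days 8 to 14. The Discussion's expectation therefore fits children already on lopinavir, not those who start it in hospital.

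**The case against.** The best defence is that the article speaks of a target and of an approximate number, and that a journal article may leave a PK sample-size justification to the full protocol. That is fair as far as it goes: the absence of such a justification is not the point here. But those words do not cover a gap of roughly 17 to 27 children on the design's own inputs (76 − 59 and 76 − 49). Limiting the target to eligible children on LPV/r makes the equality with all CLHIV harder to explain.

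The deductions are also rough. Some deaths and exits may follow sampling, the 28% and 14% average over CLHIV and HIV-exposed uninfected children, and the 10% mixes non-compliance with leaving. All of this stands, and it is why the counts are approximate. The planned analysis is population modelling, so the width ratios are only a guide.

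A reader might go further in four ways that the documents do not support:

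- **That a stated precision is overstated.** The article states no interval width, power or precision for any PK parameter.
- **That 76 can never be reached.** No cap on CLHIV enrolment is stated. With about 107 or more CLHIV, and full LPV/r use and eligibility, it could be.
- **That the sampling times contradict each other.** The eligibility text sets minimums, and the Discussion says only what is likely. Later sampling is not barred, and length of stay is not given.
- **That the sample will be mostly ART-experienced, or only a small fraction of 76.** Either needs shares that the article does not give.

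The article also discloses that sampling follows stabilization and that dolutegravir PK will be considered. It anticipates the other regimen but does not adjust the 76.

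**Conclusion.** The point holds as an inconsistency between a stated size and the article's own planning figures. At the planned 76 CLHIV, a PK sample of 76 requires no deaths or exits before sampling, universal LPV/r use and universal eligibility. Planned mortality and loss alone point to about 49 to 59 children, or about 36 to 46 at the earlier CLHIV mortality. The result assumes that CLHIV enrolment stays at 76, that most deaths and losses precede sampling, and that the planned rates apply to CLHIV. It is a modest issue in a secondary sub-study, but the shortfall is too large to pass as rounding.

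**What to change.** 1. In Study Procedures and in Data Management and Statistical Analysis, present 76 as the maximum. Give an expected evaluable number net of deaths and exits before sampling, regimen share and exclusions, with each assumed share stated.
2. State the precision which that number supports for the main PK parameters, with the assumed between-child variability.
3. Clarify how the Discussion's expected sampling week applies to ART-naive children, given the two-week minimum in Inclusion Criteria and Study Procedures and the end of follow-up at discharge.
4. Limit the PK dosing conclusions to the stabilized children on LPV/r who were sampled, rather than the study population as a whole.

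The cost is a few sentences and a less favourable stated number. No extra patients or procedures are needed.

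### Sampling every child at 3, 6 and 12 h leaves the lopinavir absorption model weakly estimated and uncheckable; staggering the same three samples would cure most of this, and would protect Cmax if peaks come before about 2 h

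*Protocol article*

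**What the plan says.** The Study Population section says that trial children with HIV on lopinavir/ritonavir "will take part in the pharmacokinetic sub-study providing 3 sparse PK samples each". Study Procedures fixes the times: after an observed morning dose, "sampling will be done at 3 h, at 6 h and at 12 h (just before the evening dose". The sentence before it shows that these times serve the whole group and not only each child: "The samples will be collected from the study population to cover three time points". The day may vary ("the samples will be taken over 2–3 days depending on what is physiologically possible for the children"), but the times after dose do not.

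The Methods paragraph of the abstract names the targets as "geometric means of steady-state LPV PK parameters", namely AUC over 0-12 h, "maximum concentration (C_max_) and concentration at 12 h after dose (C_12h"), and says that these go into PK-PD models to find optimal doses. Data Management and Statistical Analysis states that "sparse PK samples will be obtained from approximately 76 CLHIV" and that, in NONMEM, "PK-PD modeling and simulations will be performed to determine primary PK parameters, measures of plasma drug exposure and the dosing requirements".

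The article gives no Tmax, half-life, absorption rate, prior absorption model or precision target for lopinavir.

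**The concern.** A sparse population design normally works because different children are sampled at different times, so that the group covers the dosing interval even though each child gives few samples. Here the group covers only three nominal times, all at or after 3 h. What the model learns about absorption comes from indirect contrasts among those times. With three distinct times, the mean profile can support three typical-value parameters (CL, V, ka) and no more. A lag time or another absorption form cannot be told apart from simple first-order absorption.

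At stake are dose simulations that carry an unchecked absorption model and a poorly known spread of ka between children and, if peaks are early, an imprecise Cmax. A later analysis plan can choose a model or borrow a prior, but it cannot recover times that were not sampled.

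**Working it through.** The article states no precision figure for the PK parameters, so there is nothing to reproduce. The check compares the fixed schedule with a staggered one using the same number of samples.

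**From the article:** 76 children, three samples each, fixed times 3/6/12 h, 12 h dosing interval at steady state.

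**Assumed (not in the article):** one compartment with first-order absorption; half-life 3, 5 or 8 h; ka 0.3 to 1.5 per h. Two levels of variability, as log-scale SDs for CL, V, ka and residual error: 0.3, 0.3, 0.6, 0.2 (lower) and 0.4, 0.4, 0.8, 0.3 (higher). Between-day variability is not modelled.

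**Staggered comparator:** 38 children at 1/4/12 h and 38 at 2/6/12 h.

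**1. Profile.** With k = ln 2 / half-life = CL/V, C(t) is proportional to ka/(V(ka − k)) × [e^(−kt)/(1 − e^(−12k)) − e^(−ka·t)/(1 − e^(−12ka))], and Tmax = ln{ka(1 − e^(−12k)) / [k(1 − e^(−12ka))]} / (ka − k).

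Example, half-life 5 h and ka 1.2: k = 0.1386, 1 − e^(−12k) = 0.8105, and e^(−14.4) is about 0. Tmax = ln(1.2 × 0.8105/0.1386)/1.0614 = ln(7.02)/1.0614 = 1.84 h. The bracket is 0.787 at 3 h and 0.846 at Tmax, so the 3 h value is 93% of Cmax.

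**2. Precision.** First-order population Fisher information. For each child, F is the matrix of derivatives of log C with respect to log CL, log V and log ka, and S = FΩF' + σ²I. Information on typical values is the sum of F'S⁻¹F. For the variances it is the sum of ½ tr(S⁻¹DₐS⁻¹D_b), where D is the derivative of S with respect to each variance. RSEs come from the inverse; that of Cmax uses the delta method.

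Ranges run over the three half-lives and both variability levels. RSEs are in %, fixed / staggered.

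| ka (per h) | Tmax (h) | highest of C3, C6, C12 as % of Cmax | RSE Cmax | RSE ka | RSE variance of ka | RSE CL |
|---|---|---|---|---|---|---|
| 0.3 | 3.25-3.91 | 98.8-99.8 | 3.6-5.3 / 3.6-5.1 | 43.3-94.4 / 35.5-74.0 | 109-189 / 85-159 | 3.7-5.0 / 3.8-5.2 |
| 0.6 | 2.41-2.92 | 98.0-100 | 3.8-6.3 / 3.5-5.0 | 16.3-40.6 / 11.8-26.8 | 54-142 / 32-74 | 3.7-5.2 / 3.8-5.2 |
| 0.8 | 2.07-2.50 | 94.1-99.3 | 4.3-7.3 / 3.4-5.0 | 16.2-45.0 / 10.7-24.1 | 85-230 / 34-74 | 3.8-5.4 / 3.7-5.1 |
| 1.0 | 1.82-2.20 | 89.8-97.9 | 5.4-9.3 / 3.4-5.0 | 19.6-58.6 / 10.8-24.2 | 143-443 / 40-81 | 3.9-5.9 / 3.7-5.1 |
| 1.2 | 1.63-1.97 | 85.7-96.3 | 7.4-12.7 / 3.4-5.1 | 26.5-83.7 / 11.5-25.6 | 210-897 / 45-90 | 4.3-6.9 / 3.7-5.1 |
| 1.5 | 1.42-1.71 | 80.4-94.0 | 13.4-22.5 / 3.4-5.3 | 48.1-157.9 / 13.0-28.9 | 296-2461 / 54-108 | 5.7-10.3 / 3.7-5.1 |

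Regrouped by Tmax, the fixed-design RSE of Cmax is 3.6-6.3% at 2.4 h or later, 4.5-12.7% at 1.63-2.33 h with ka up to 1.2, and 13.4-22.5% at 1.42-1.71 h with ka 1.5. An RSE above 100% means that the quantity is in practice not estimated.

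**3. Can the model form be checked?** Concentrations at 3, 6 and 12 h were generated without a lag (half-life 4 or 6 h, ka 0.5, 0.8 or 1.2), then refitted with lags of 0 to 2 h. Every lag reproduced the three values exactly. The fitted ka rose up to 3.4-fold (0.50 to 1.68), AUC fell to as low as 0.78 of its true value, and Cmax ranged from 0.91 to 1.04 of its true value. The data cannot choose among these fits.

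**The case against.** The strongest reply is that ka is not a reported target. The named measures are AUC, Cmax and C12h, and a poor ka does not by itself make Cmax poor. That stands. A reader might infer that Cmax is badly identified because nothing is taken before 3 h, but the article does not support that: it gives no Tmax, and with a peak at about 2.4 h or later the fixed times do nearly as well as staggered ones. The column for the highest sampled concentration is also only descriptive, since the planned analysis is model-based and does not read Cmax off the data.

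Three other inferences go too far. The toxicity worry in the Discussion concerns free drug when albumin is low, not the peak. The Introduction's remark on bioavailability need not mean the rate of absorption; extent acts through apparent clearance and AUC. And the spread over 2-3 days does not show that any sampled dose is unobserved, since the sentence on the observed dose can be read as applying to each PK day.

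It is also fair that a condensed article may leave an absorption prior and the recording of actual times to a full PK plan, and that the study builds on earlier lopinavir/ritonavir work. A prior could stabilise the fit, but three fixed times would still not let the data test it in severely malnourished children. A staggered scheme that dropped the 12 h sample in some children would weaken C12h and lean on the previous evening's dose; the scheme used here keeps 12 h in every child.

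**Conclusion.** The point holds as a design weakness of the sub-study. With three common times from 3 h onward, ka, its between-child variance and the absorption form are weakly estimated and cannot be verified, although the model is meant to inform dosing. At ka 0.8-1.2 per h the RSE of the ka variance is about 85-900% fixed against 34-90% staggered.

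For Cmax the point is conditional. The loss is small if Tmax is about 2.4 h or later (about 4-6%), moderate at about 1.6-2.3 h (4-13%), and material at about 1.4-1.7 h (13-23%), against 3-5% with staggering over the whole range. CL precision, and so AUC precision given the right model, is the same or better with staggering, apart from a difference of at most 0.2 percentage points when absorption is slow. Staggering does not rescue everything: at ka 0.3 the RSE of ka is still 36-74%.

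These figures rest on the assumed model, half-lives, absorption rates and variability, and on reaching 76 children. With n children they grow by about √(76/n). The randomized mortality comparison is not affected.

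**What to change.** Keep three samples per child and keep the 12 h sample in all. Allocate children by a prepared list to two sets of earlier times, for example half at about 1 and 4 h and half at about 2 and 6 h. The group then covers five times instead of three, which also allows a lag or another absorption form to be tested. On each PK day, record the actual clock times of doses and samples, if the full protocol does not already require it. If 3/6/12 h is kept, state the assumed Tmax or the prior absorption model that justifies it.

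Cost: a change to the wording of the sampling schedule, an allocation list, and staff following two schedules. There are no extra draws, assays or children. The change has to come before sampling, because it cannot be made up afterwards for children already sampled.
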